## Abstract

**Background:**

Breast cancer is the second most common cancer in women worldwide. Treatments for this disease often result in side effects such as pain, fatigue, loss of muscle mass, and reduced quality of life. Physical exercise has been shown to effectively mitigate these side effects and improve the quality of life in patients with breast cancer.

**Objective:**

This randomized clinical trial aims to evaluate the efficacy of a 12-week supervised exercise program on pain, physical function, and quality of life in female patients with cancer.

**Methods:**

This randomized, double-blind clinical trial will recruit 325 participants, divided into an intervention group receiving the exercise program and a control group receiving standard care recommendations. Outcome measures, including pain (assessed via the Brief Pain Inventory), physical function (Disability of the Arm, Shoulder, and Hand Questionnaire), and quality of life (European Organization for Research and Treatment of Cancer QLQ-C30 and European Organization for Research and Treatment of Cancer QLQ-BR23), will be evaluated at baseline, immediately post intervention, and 12 weeks post intervention. Statistical analysis will involve repeated measures of ANOVA and MANOVA to determine the significance of the intervention’s effects across time points.

**Results:**

Recruitment and data collection will commence in February of 2025, and data analysis is scheduled for completion at the end of 2025. No results are currently available

**Conclusions:**

Physical exercise is anticipated to play a significant role in alleviating pain, enhancing physical function, and improving the quality of life in female patients with cancer. This study will provide robust evidence to support the integration of supervised exercise into standard care protocols for this population.

**Trial Registration:**

ClinicalTrials.gov NCT06618690; https://clinicaltrials.gov/ct2/show/NCT06618690

**International Registered Report Identifier (IRRID):**

PRR1-10.2196/63891

## Introduction

### Background

The World Health Organization (WHO) defines breast cancer as a pathology in which cells present in the breast reproduce uncontrollably and form tumors [1]. It is the second most common type of cancer worldwide, with an incidence in 2022 of 2.3 million. Similarly, in 2022, its mortality rate ranked fourth in the world with a rate of 669,418 [2]. Women are the most affected by this disease, with only 0.5% to 1% of cases in men [1].

Genetic mutations play a key role in cancer development. Mutations in *BRCA1* and *BRCA2* increase the risk of breast [3], ovarian, and prostate cancers, while *TP53* is linked to multiple cancers like breast and colon due to its role in cell cycle regulation [4]. *PTEN* mutations are found in breast and thyroid cancers [5], and APC is associated with colorectal cancer [6]. *MLH1* and *MSH2* mutations cause Lynch syndrome, increasing colorectal cancer risk [7]. *KRAS* mutations are common in lung, colon, and pancreatic cancers [8].

Other causes of the disease are diverse: on the one hand, advanced age at motherhood and late menopause are also considered risk factors. On the other hand, breastfeeding, physical exercise and not consuming alcohol are considered protective factors against the disease [9,10].

Treatment will be selected according to the characteristics of the tumor. Generally, it is based on neoadjuvant or adjuvant chemotherapy, radiotherapy, surgery, and hormonal therapy [11].

The prognosis of the disease has improved due to early diagnosis and therapeutic advances. The mortality rate, in turn, has decreased significantly [12,13]. Because of this increase in survival, scientific society is becoming interested in the treatment of the side effects that these patients may suffer, which include both physical and psychological symptoms [14]. Associated physical symptoms that may appear include lymphedema, decreased movement and strength of the upper limb, decreased mobility and strength of the upper limb [15], pain [16], bone loss [17], and sarcopenia [18].

These side effects have a direct impact on the health-related quality of life of patients with cancer [14]. The WHO defines quality of life as the individual’s perception of his or her social and cultural way of life, as well as his or her expectations and goals. This is a very open concept that encompasses different aspects of the person from physical health, psychological state, level of independence, social relationships, and personal beliefs [19]. Quality of life measurement is frequently used in breast cancer studies to evaluate the effectiveness and outcomes of treatments [20].

### Exercise and Breast Cancer

It has been observed that patients with breast cancer present atrophy of the skeletal muscle apparatus, which is associated with the mitotoxic effects of chemotherapy. Anthracyclines, substances that play a leading role in chemotherapy against breast cancer, have an affinity for the inner membrane of the mitochondria, the place where the body’s energy is produced; therefore, this mechanism explains fatigue, atrophy, and muscle pain [21,22].

Various treatments are currently being studied to alleviate these side effects, including therapeutic exercise. Exercise provides short- and long-term benefits to reduce the symptoms that may appear during treatment in each patient. Here, therapeutic exercise specialists play an important role in helping patients overcome their fear and improve their physical abilities [23]. The American College of Sports Medicine says exercise is associated with improved survival after developing cancer [24].

The health professionals in charge of applying this type of therapy must evaluate each patient individually and adapt the exercise prescription to each one of them. The ideal type of exercise for these patients is one that includes a combination of aerobic and resistance exercise, the intensity of each of these parts will be determined by the characteristics of the patient [25,26].

There is evidence that professionally supervised physical exercise has positive results compared to unsupervised exercise. Research has shown evidence that it positively influences decreases anxiety, depressive symptoms, and fatigue, improves quality of life and physical function, and there is no risk of exacerbating upper limb lymphedema. Even people who have already developed lymphedema can perform resistance exercises. In 2000, Harris and Niesen-Vertommen [27] were the first to start strength studies with people with lymphedema, as the existing recommendations so far were the rest of the affected limb [27-30].

The objective of this project is to develop a randomized clinical trial to determine the efficacy of a supervised exercise program on pain, physical function, and quality of life in female patients with cancer.

## Methods

### Hypothesis

A supervised exercise program reduces pain and improves physical function and quality of life in female patients with cancer compared to a control group not receiving the exercise program.The beneficial effects of the supervised exercise program are maintained over time at least 12 weeks after the end of the program.

### Study Design

This study will be a single-blind, randomized clinical trial. To determine the efficacy of a therapeutic exercise program on the different dimensions of quality of life, physical function, and pain in patients with cancer. Once the participants have been recruited, they will be randomly assigned to 2 groups (intervention group and control group). Three assessments will be made: initial assessment, assessment after the end of the intervention, and assessment 12 weeks after the end of treatment. The intervention group will follow a 12-week therapeutic exercise plan, and the control group will follow the usual recommendations for this type of patient. After this last assessment, the participants in the control group will be offered the intervention. (Figure 1). Approval will be sought from the ethics committee of the University Hospital of Torrecárdenas.

**Figure 1 figure1:**
[figure not shown]
Untitled.

### Study Population

The participants will be recruited through the oncologists of the University Hospital of Torrecárdenas. The inclusion criteria will be the following: women aged between 45 and 65 years (age range with the highest incidence in Spain), with oncologic treatment completed less than 3 months ago, without metastasis, without pathologies that contraindicate exercise, and who have agreed to sign the informed consent form. The exclusion criteria will include: not attending scheduled sessions to instruct on the exercises to be performed, being part of other studies, undergoing another type of therapy, and pregnant patients.

The selected age range of 45 to 65 years for participants is based on epidemiological data indicating that this demographic encompasses the highest incidence of breast cancer in Spain. This range ensures a representative sample for evaluating the intervention's efficacy while excluding populations less likely to face similar diseases and treatment dynamics. Additionally, menopause is included as an independent variable in the analysis due to its significant influence on both physiological and psychological responses to breast cancer treatment and exercise interventions. Hormonal changes associated with menopause can affect musculoskeletal health, fatigue levels, and overall quality of life, making it a critical factor to consider when evaluating the intervention’s outcomes on pain, physical function, and quality of life [31]. By accounting for these variables, the study aims to provide a nuanced understanding of how menopausal status may modulate the benefits of supervised exercise in patients with cancer.

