### Intervention

The proposal will be carried out in the intervention group (group 1), while the control group (group 2) will undergo the conventional recommendations indicated for this type of patient.

A supervised training plan will be carried out for 12 weeks with a frequency of 3 sessions per week with a duration of 60 minutes, an ideal estimate according to the meta-analysis of Montaño-Rojas et al [48]. In first 2 weeks, the group exercises will be performed to familiarize the participants with the exercises and then each participant will perform them at home with a review every 2 weeks to assess the increase of the load.

The exercises and loads included in this treatment plan have been designed and modified based on previous clinical trials [39,49-51]. The training plan will work the upper limbs, lower limbs, and trunk. All sessions begin with a general warm-up, which will be previously instructed to the participants, in which the heart rate will be increased (Multimedia Appendix 2). After a 2-minute break, the specific block of each session will begin (Textbox 1 and Multimedia Appendix 2). All exercises will be performed with dumbbells, elastic bands, and a ball. We will consider the age of each participant, making minor adjustments to the initial exercise program as needed.

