Three sets of all exercises will be performed with 10-12 repetitions at 50%-60% 1 MR (previously calculated for each participant in each of the exercises) with 1 minute of rest between sets. Finally, we will conclude with general stretching previously instructed (Multimedia Appendix 2). The control group will participate in a general education and wellness program designed to promote overall well-being and maintain a basic level of activity. This program, matched in duration to the experimental group, will include regular counseling sessions covering topics such as nutrition, stress management, sleep quality, and relapse prevention. In addition, participants will be encouraged to engage in low-impact physical activities, such as short walks and gentle mobility exercises. For the experimental group, the supervised exercise program aims to improve pain, physical function, and quality of life through a variety of carefully selected exercises tailored to each participant’s needs. These include stretching exercises, such as pectoral stretches for chest mobility and shoulder and arm stretch to enhance the range of motion and relieve tension. Strength training exercises using resistance bands or light weights will focus on improving upper limb and core strength to enhance posture and stability. Aerobic activities like walking or stationary cycling will be incorporated to boost cardiovascular endurance and mobility. Flexibility exercises, including range-of-motion activities, will help maintain and improve overall flexibility, while balance and coordination exercises will enhance stability and prevent falls. Muscle endurance will also be developed through lightweight or resistance band exercises. The program's design emphasizes a personalized approach, guided by physiotherapists or exercise specialists, to ensure safety and maximize benefits for patients with cancer.

Strength exercises included in the training plan.

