### Data Management and Analysis

Once all the measurements included in the measuring instruments section have been taken, they will be recorded and analyzed using SPSS (version 28.0; IBM Corp) [52].

The quantitative data of the sample will be described by number, mean, and SD.

A result is understood to be significant when *P*≤.05. In statistics, significance or internal consistency indicates that there is congruence between the different results obtained [53].

For the statistical analysis of the results of this test, 2 tests will be performed as follows.

Repeated measures ANOVA: This analysis allows us to evaluate whether the differences between the results of the same test in a participant are statistically significant. If so, it also determines what percentage of the effect is attributable to the intervention and not to other factors [53]. Two ANOVA analyses will be performed: one comparing the preintervention assessment with the postintervention assessment, and the other comparing the postintervention with the assessment 12 weeks later. This test will check if there is a significant improvement in the different measures of pain, physical function, and quality of life. Finally, the paired comparison table will tell us in which measurement periods the differences are found [53].ANOVA of differences: In this case, the differences between the results of the intervention group and the control group will be compared [53]. With the results obtained from this statistical analysis, it will be possible to verify whether the differences between groups in terms of pain, physical function, and quality of life are significant between the participants receiving the intervention and those belonging to the control group.MANOVA: To assess the overall effect of the intervention and determine whether the hypotheses can be accepted or refuted, the following hypotheses will be tested [53].

These statistical analyses described the significance between the test results of the same individual and the significance between the different results of both groups of the test that will be tested.

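### Non-attendance at exercise instruction is an exclusion criterion that appears to act after randomisation and in the exercise arm only

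*Protocol article*

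**What the plan says.** All of this is in the protocol article.

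- **Study Population** lists among the exclusions: "The exclusion criteria will include: not attending scheduled sessions to instruct on the exercises to be performed". It does not say when these sessions take place or who is invited to them.
- **Study Design** puts assignment straight after recruitment: "Once the participants have been recruited, they will be randomly assigned to 2 groups". It describes no run-in and no teaching before randomisation. Controls are offered the intervention only after the last assessment.
- **Intervention** gives the programme to one arm: "The proposal will be carried out in the intervention group (group 1), while the control group (group 2) will undergo the conventional recommendations". Scheduled group teaching comes at the start of the 12-week plan: "In first 2 weeks, the group exercises will be performed to familiarize the participants with the exercises". After that the women train at home, with a review every 2 weeks.
- **Intervention**, on the control programme, says that it "will include regular counseling sessions covering topics such as nutrition, stress management, sleep quality, and relapse prevention", and that "participants will be encouraged to engage in low-impact physical activities, such as short walks and gentle mobility exercises". No attendance requirement is attached to the counselling.
- **Data Management and Analysis** says of the between-group test that "the differences between the results of the intervention group and the control group will be compared". Nothing there keeps excluded women in the comparison.

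**The concern.** An exclusion criterion should be a fact that can be settled before assignment and that any candidate can meet or fail. Attendance at sessions belonging to one arm's programme is neither. It is adherence, observed after randomisation. A control woman with the same fatigue, pain or low motivation has no exercise-instruction session to miss, so she cannot fail the item.

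If the rule is applied, the exercise arm loses some women on a ground that has no counterpart among controls. Attendance plausibly depends on the same things that drive pain, function and quality of life, all of which are measured by patient-reported questionnaires. The balance that randomisation creates would then be disturbed in one arm, and the difference between groups would mix the effect of exercise with the effect of selection. If excluded women are also not followed up, no later analysis can recover their outcomes.

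**Working it through.** **Step 1: can a control woman fail the criterion, and can anyone fail it before assignment?**

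| Question | Where the article answers | Answer |
|---|---|---|
| When is assignment? | Study Design | After recruitment, with no prior instruction described |
| When is scheduled group teaching? | Intervention | First 2 weeks of the 12-week plan |
| Who gets it? | Intervention | Intervention group |
| What do controls attend? | Intervention | Counselling sessions |
| Is there an attendance rule for controls? | Study Population, Intervention | None stated |

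The sections agree with one another. Together they place the criterion after randomisation and in one arm. This is a reading across sections, because the criterion itself is silent on timing and arm.

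**Step 2: how large could the effect be?** The plan has no figure of its own for this, so there is none to reproduce. The calculation is an illustration.

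Inputs from the Sample section: 280 participants before the dropout allowance, so 280/2 = 140 per arm; two-sided α = 0.05; planned effect 0.5, read as SD units; attrition 15%. The 280 is used only as the plan's stated size. Whether it follows from its own inputs is a separate matter.

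Assumed, not in the documents:
- p, the share of the exercise arm excluded, from 5% to 15%. The top is set at the plan's own attrition figure.
- D, the mean of attenders minus the mean of non-attenders on the analysed outcome (or on its change, if changes are analysed), in SD, with higher meaning better. The range is 0.2 to 0.5, with 1.0 as a pessimistic case.

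Formulas, under no true effect and a normal approximation:
- Bias = p × D, the amount by which the attenders' mean exceeds the mean of the whole arm.
- SE = √[1/(140(1−p)) + 1/140].
- Two-sided error = P(Z > 1.96 − bias/SE) + P(Z < −1.96 − bias/SE).

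Worked case, p = 0.15 and D = 0.5:
- Bias = 0.15 × 0.5 = 0.075 SD.
- SE = √(1/119 + 1/140) = 0.1247.
- Bias/SE = 0.602.
- Error = 0.0872 + 0.0052 = 0.092.

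| p | D (SD) | Bias (SD) | Two-sided error |
|---|---|---|---|
| 5% | 0.2 | 0.010 | 5.1% |
| 5% | 0.5 | 0.025 | 5.5% |
| 10% | 0.2 | 0.020 | 5.3% |
| 10% | 0.5 | 0.050 | 6.9% |
| 15% | 0.2 | 0.030 | 5.7% |
| 15% | 0.5 | 0.075 | 9.2% |
| 15% | 1.0 (pessimistic) | 0.150 | 22.5% |

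Against the planned effect of 0.5, the main range is 0.01/0.5 = 2% to 0.075/0.5 = 15%. The pessimistic case is 0.15/0.5 = 30%.

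Starting from about 162 per arm (325/2) changes little: 15% and 0.5 SD gives 9.9% instead of 9.2%. A larger trial makes the same bias slightly more likely to reach significance.

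**Step 3: without the rule.** If every randomised woman is kept in her assigned arm and her outcomes are collected, the bias from this source is 0 and the error stays at 5%.

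**The case against.** **Timing and arm are inferred.** The criterion states neither, and the flow diagram in Figure 1 is not available here. The Intervention section also speaks of a warm-up and stretching taught beforehand and of maximum-repetition loads measured beforehand, so there may be teaching outside the group sessions. This stands as a limit on certainty. But no section places any teaching before randomisation, and doing so would show the exercises to women whom the Hypothesis section describes as not receiving the programme. If that was the intention, the text still needs to say so.

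**The analysis set may be defined elsewhere.** An article can leave that to a statistical analysis plan, and its absence here is not the fault. The article makes no explicit intention-to-treat commitment, and it does not say that non-attenders lose follow-up or leave the dataset. This also stands, which is why the conclusion is that the groups may no longer be the randomised ones. The fault on the page is the eligibility rule itself.

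**The attrition allowance covers it.** It does not. Recruiting more women protects power but does not undo selection in one arm.

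**Stronger readings that a reader might infer.**
- That controls are all retained. They are not: the other exclusions and general attrition can affect either arm. Only this one item lacks a control-arm counterpart.
- That bias towards exercise is established. It is the plausible direction, but the article has no data on how non-attenders differ.
- That the error could reach about one half. This needs 25% excluded and a 1.0 SD gap. The first exceeds the plan's 15% attrition for the whole trial. The second is a gap in outcome level, much of which would cancel if the planned ANOVA of differences analyses changes from baseline, a point the wording leaves open. With 15% excluded and a 0.2 SD difference in change, the error is 5.7%.

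**Conclusion.** The point holds. As written, an eligibility item treats non-adherence as ineligibility, apparently after randomisation and only in the exercise arm, and nothing else in the article neutralises it. That structural fault does not depend on any assumed number.

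The consequence is likely, not proven, to favour exercise. Its size is unknown. For 5% to 15% excluded and a gap of 0.2 to 0.5 SD, the bias is 0.01 to 0.075 SD and the two-sided error 5.1% to 9.2%; the pessimistic case of 15% and 1.0 SD reaches 22.5%. At the low end the distortion is negligible, and at the high end it would matter for the claim. These figures assume no true effect, 140 women per arm, and that excluded women are missing from the comparison.

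It should be corrected before any woman is excluded under the rule, because uncollected outcomes cannot be restored.

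**What to change.** 1. Delete non-attendance at instruction sessions from the exclusion criteria, so that the list holds only facts known before assignment.
2. State that every randomised woman is invited to both follow-up assessments (after the intervention and 12 weeks later) and is analysed in her assigned arm whatever her attendance.
3. Record attendance as adherence, and use it only in a supportive analysis.
4. If a check of commitment is wanted, apply it to all candidates before randomisation, in the same way whichever arm they later enter.

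The cost is one eligibility line, one sentence on analysis, and the effort of assessing non-attenders. The downside is that the estimated effect may be somewhat smaller, because women who did not attend are counted.
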